### Study Setting

This study will be carried out in the outpatient clinic of the Department of Dermatology in an academic center in the Netherlands (Radboud University Medical Center, Nijmegen). This department is a national psoriasis expertise center. Patients will initially be screened at the Department of Dermatology for signs or symptoms of enthesitis, dactylitis, arthritis, or inflammatory back pain by a trained rheumatologist. When additional rheumatological evaluation is required, patients are preferentially referred to the Department of Rheumatology of the Sint Maartenskliniek in Nijmegen. Here, the patient will be assessed by a rheumatologist with special expertise in PsA. When requested by the patient, a referral to another rheumatologic center is also possible.

### Participants

All patients with a clinical diagnosis of psoriasis who are treated at the outpatient clinic are eligible for this study. Neither current nor previous treatment by a rheumatologist nor a previous diagnosis of PsA are exclusion criteria. Patients must be 18 years or older and be able to give written informed consent.

#### Study Size

For the logistic model, we aim to use 5 to 10 independent variables. The number of independent variables used in the model will be restricted to 1 per 10 events (ie, 1 per 10 PsA cases). Therefore, we aim to have 50 to 100 PsA cases. Assuming a prevalence of PsA of 20% to 30% [1], this means we need 167 (prevalence 30%, 5 predictors) to 500 (prevalence 20%, 10 predictors) patients with psoriasis. Using a total number of 300 patients, we expect to find up to 60 to 90 PsA cases, ensuring we can incorporate 6 to 9 independent variables.

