### Design

The DAPPER study is a monocenter observational study with a follow-up of 1 year. We will examine 300 patients stratified 1:1:1 according to current dermatological treatment (topical or UV therapy only, conventional systemic medication but no biologicals, biological therapy).

The initial screening at the dermatology department will include a 68 tender joint count, 66 swollen joint count, a dactylitis count (0-20), and enthesitis scores (Leeds Enthesitis Index [LEI] [19] and the enthesitis score of the Spondyloarthritis Research Consortium of Canada [SPARCC] [20]). Inflammatory back pain will be assessed via the criteria of the Assessment of Spondyloarthritis International Society [21]. At this study visit, no laboratory tests or imaging will be performed for diagnostic purposes.

To investigate possible identifying characteristics or confounders for the detection of PsA, the study visit will also be used to gather demographical data (comorbidity, treatment data, and clinical characteristics of the skin). An example of the interview guide used is shown in Multimedia Appendix 1.

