#### Possible Identifying Characteristics for the Presence of PsA in Psoriasis

The identifying value of various clinical markers for the presence of PsA in psoriasis will be processed as independent variables in a univariate logistic regression model. Diagnosis of PsA (yes/no) will be the dependent variable. Variables that are statistically related to the outcome (*P*≤.20 in univariate modeling) and are clinically and methodologically feasible (based on a favorable balance between prevalence in the cohort, effect size, and ease of measurement) will be selected. The subsequent selection of variables will be tested in a multivariable logistic regression model with backward stepwise selection. Sensitivity analysis will be performed by reclassifying patients with an uncertain diagnosis as cases. The number of possible independent variables will be limited based on a minimum of 10 events (PsA diagnoses) per variable. Bootstrapping will be used to assess the internal validity of the model in terms of overoptimism and shrinkage.

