## Discussion

PsA is an inflammatory disease of joints and entheses, which can cause pain, disability, and a diminished quality of life. Moreover, prolonged arthritis can lead to permanent irreversible joint damage [6,7]. Early recognition, for example, by screening populations at high risk for PsA, may be able to prevent joint damage by facilitating timely treatment. The high prevalence of PsA in patients with psoriasis and the fact that skin complaints mostly appear years before joint involvement make this population suitable for the implementation of screening. However, current screening questionnaires are not sufficient. Therefore, we wish to determine if current screening and referral strategies are satisfactory, and to improve them if necessary.

In our study, we used three of the previously developed questionnaires: PASE, PEST, and ToPAS [13-15]. Although their sensitivity and specificity could be improved, we feel that the possibly identifying variables used in these questionnaires warrant further evaluation [17,18]. Our study has several strengths that may overcome the suboptimal performance of the beforementioned questionnaires. First, the PASE and PEST development studies were hampered by a low amount of PsA cases (17 and 12, respectively) [13,14]. Second, the setting of our study in the Dermatology Department ensures access to the target population with minimal extra burden for the patient. Although the ToPAS study included 164 patients with PsA, most of these were recruited via the Rheumatology Department. Only 123 study participants were recruited via the Dermatology Department, giving rise to 30 PsA cases [15]. As stated in the study size, we expect to find 60 to 90 PsA cases in our cohort. Therefore, we expect our model to be more precise.

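### Study Size presents 6 to 9 predictors as ensured by 300 patients, but that is only the expected yield; separately, the 10-event cap counts variables rather than estimated coefficients

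*Protocol article*

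**What the plan says.** Under Study Size, the protocol article sets the aim of the logistic model: "we aim to use 5 to 10 independent variables", hence 50 to 100 PsA cases. The cap is "The number of independent variables used in the model will be restricted to 1 per 10 events (ie, 1 per 10 PsA cases". With an assumed prevalence of 20% to 30%, the article concludes that "this means we need 167 (prevalence 30%, 5 predictors) to 500 (prevalence 20%, 10 predictors) patients with psoriasis". It then settles on 300 patients and says that "we expect to find up to 60 to 90 PsA cases, ensuring we can incorporate 6 to 9 independent variables".

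The Statistics section on identifying characteristics repeats the cap: "The number of possible independent variables will be limited based on a minimum of 10 events (PsA diagnoses) per variable". Both places count variables. Neither mentions coefficients, and neither gives a margin or assurance level around the expected number of cases.

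The section on identifying characteristics under Outcome Variables lists current and previous treatment among the data to be collected. Under Design, current treatment has three groups: "topical or UV therapy only, conventional systemic medication but no biologicals, biological therapy".

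**The concern.** Two separate matters are at issue.

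The first is the word used for the result. One sentence treats the same case count as an expectation, as a ceiling (through the words *up to*) and as a guarantee. A mean cannot be guaranteed, and this sentence is the only support given for the number of patients. A reader would take 6 predictors at the low prevalence, or 9 at the high one, as secure.

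The second is the unit of the cap. Overfitting in a logistic model is driven by the number of coefficients estimated. A categorical predictor with k levels needs k-1 of them, and a non-linear term adds more. A cap that counts each such predictor once is looser than the 10-events rule it appears to apply. The model is meant to lead to a referral tool, so the limit on its size should mean what it says.

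**Working it through.** **Inputs.** From Study Size: N = 300; prevalence p = 20% to 30%; 10 PsA cases per variable; aim of 5 to 10 variables. From Design: current treatment in three groups.

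**1. The plan's own figures.** N needed = 10 × variables / p.
- 5 variables at 30%: 50 / 0.30 = 166.7, rounded up to 167.
- 10 variables at 20%: 100 / 0.20 = 500.
- Expected cases with 300 patients: 300 × 0.20 = 60 and 300 × 0.30 = 90.
- Variables: 60 / 10 = 6 and 90 / 10 = 9.

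All of these reproduce. The arithmetic is correct.

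**2. How likely the expected yield is.** Take the number of cases X as Binomial(300, p), with SD = √(300 × p × (1 − p)).

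| | p = 20% | p = 30% |
|---|---|---|
| Mean (SD) | 60 (6.9) | 90 (7.9) |
| P(X at or above the mean) | 0.523 | 0.522 |
| P(X ≥ 50), the minimum aim | 0.938 | above 0.999 |
| P(X ≥ 100), the upper aim | below 0.001 | 0.116 |

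**3. What a stated assurance level would support.** Find the largest r with P(X ≥ r) at or above the level, then divide by 10 and round down.

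| Assurance | p = 20% | p = 30% |
|---|---|---|
| 95% | 49 cases, 4 | 77 cases, 7 |
| 90% | 51 cases, 5 | 80 cases, 8 |
| 80% | 54 cases, 5 | 83 cases, 8 |

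Levels of 97.5% and 99% also give 4 and 7. None of the levels tried, from 80% upwards, gives 6 and 9.

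**4. The upper aim.** 100 cases among 300 patients needs a prevalence of 100 / 300 = 33.3%, above the assumed range.

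**5. Variables against coefficients.** Let one of the variables be the three-group treatment and let each of the others use one coefficient.
- 6 variables, 60 cases: 5 + 2 = 7 coefficients, and 60 / 7 = 8.6 events per coefficient.
- 9 variables, 90 cases: 8 + 2 = 10 coefficients, and 90 / 10 = 9.0 events per coefficient.

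Both models obey the cap as written and fall below 10 events per coefficient. Each further multi-level or non-linear predictor lowers the ratio again. Step 5 does not depend on steps 2 and 3: it holds even if exactly the expected number of cases is found.

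**The case against.** The strongest reply is that the plan corrects itself. The cap is tied to observed PsA cases in both places, so a low yield gives a smaller model and not an overfitted one. This stands, and it confines the first matter to the stated figure. A reader might infer that the fitted model will hold more variables than the rule allows; the documents do not support that.

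A second reply is that the plan sets no assurance level, so 4 to 7 is a reviewer's choice. This also stands. The 4 is close to the edge (49 cases against 50), and at 80% to 90% the range is 5 to 8. The 52% applies only at the ends of the prevalence range: at 25%, the chance of at least 60 cases is 98%. The minimum aim of 50 cases is likely to be met even at 20% (94%). The aim of 5 to 10 variables is no contradiction either, since 300 lies between 167 and 500 and the text discloses the resulting 6 to 9.

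A third reply is that coding may be left to a fuller document, and that bootstrapping and later external validation are planned. Coding can indeed be settled elsewhere. But the unit of the cap is fixed here, twice, as variables. Bootstrapping measures optimism; it does not change what the cap permits.

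A reader might also turn the Discussion's "Therefore, we expect our model to be more precise" against ToPAS, given its 164 PsA cases. The text does not clearly make that comparison. It acknowledges that "Although the ToPAS study included 164 patients with PsA, most of these were recruited via the Rheumatology Department" and then points to the 30 cases recruited through dermatology. Against 17, 12 and 30 cases, 60 to 90 is a fair basis for the statement.

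**Conclusion.** The concern holds in two limited parts.

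First, 300 patients do not ensure 6 to 9 variables. That is the expected number, and at each end of the prevalence range the matching count is reached with a probability of only 52%. The aim of 100 cases is not the expected yield at any prevalence the plan assumes. The fault lies in the claim: neither the arithmetic nor compliance with the cap is affected.

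Second, and of more practical weight, the cap counts variables. With the three-group treatment as the only multi-level predictor, a model that follows the rule has 8.6 to 9.0 events per coefficient at the expected yield.

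The probabilities assume independent patients, a usable diagnosis in all 300, and a prevalence of exactly 20% or 30%. Uncertain diagnoses or losses would lower the yield; fixed treatment strata would reduce its variance slightly. The coefficient example assumes that treatment is retained and coded as three groups, which the article does not specify. Two further inferences are not supported. One is that 4 to 7 is a property of the design: it depends on the assurance level chosen and owes nothing to the coefficient point. The other is any particular loss of calibration in new patients, which would need effect sizes and coding that the article does not give.

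**What to change.** In Study Size, describe 6 to 9 as the expected number of variables, remove the claim that it is ensured, and drop the words *up to*. Add the shortfall at a stated assurance level, for example: with 95% probability at least 49 cases (prevalence 20%) or 77 cases (prevalence 30%), supporting 4 or 7 coefficients. Note there that 100 cases would need a prevalence of 33.3%.

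In Study Size and in the Statistics section on identifying characteristics, word the cap as at least 10 observed PsA cases per estimated coefficient. A k-level variable counts k-1, and each non-linear term counts one.

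No new data are needed. The cost is a less favourable stated number and possibly a slightly smaller model. The second edit matters more, because it changes what may be fitted.

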#### Recruitment

All patients eligible for the study will be asked for study participation by their dermatologist. Written and oral information about the study will be given by the investigator. A study visit will be planned adjacent to a regular outpatient visit with the dermatologist. Before the study visit starts, written informed consent is obtained from the patients.

### Outcome Measures

The primary outcome measure will be the percentage of investigated patients with the diagnosis of PsA. This diagnosis will be accepted if it was confirmed by a rheumatologist in correspondence. Fulfillment of Classification Criteria for Psoriatic Arthritis (CASPAR) is not required [23]. After 1 year, patient files of the referred patients will be checked to confirm the diagnosis. If the suspicion of active PsA is confirmed, treatment changes and their effect on disease activity will be noted. Alternatively, the other rheumatological diagnosis will be noted.

In the referred patients with PsA, HR-QoL will be assessed via two disease-specific questionnaires at referral and 1 year thereafter. Skin-related impact will be explored via the Dermatological Life Quality Index (DLQI) [24]. Joint-related impact will be explored via the Psoriatic Arthritis Impact of Disease (PsAID) [25].

### Outcome Variables

#### Prevalence of PsA

To ascertain the presence of PsA, we will ask the patient about joint and enthesis complaints (location, pattern, and intensity), morning stiffness (duration), and whether or not they ever had a diagnosis of arthritis. For confirmation of arthritis, dactylitis, or enthesitis, we will perform joint counts (swollen, tender, and dactylitis) and enthesitis indices (LEI and SPARCC). After referral, the diagnosis of PsA or alternative diagnosis will be retrieved from (the correspondence gathered in) the electronic patient file.

#### Effect of Referral

In referred patients with confirmed PsA, we will retrieve data at time of referral and 1 year later. We will use the PASDAS as a disease activity score, which gives a full overview of the PsA disease spectrum. We will evaluate both the combined disease activity score and the specific scores of tender and/or swollen joints, dactylitis, and enthesitis. In addition, treatment changes (either instigated by rheumatologist or dermatologist) will be retrieved from the electronic patient file. Impact on HR-QoL will be assessed by questionnaires before referral and after 1 year (DLQI [24], PsAID12 [25]).

#### Possible Identifying Characteristics for the Presence of PsA in Psoriasis

We will gather information about demographic variables, comorbidity, intoxications, and family history. Family history and comorbidity will be targeted at diseases that are associated with spondyloarthritis, such as uveitis, psoriasis, and inflammatory bowel disease. Next to that, the Charlson Comorbidity Index [26] and Functional Comorbidity Index [27] will be used to evaluate a total comorbidity burden. Data about comorbidity specifically associated with either psoriasis or PsA (eg, hepatic [28], psychological [29], and cardiovascular [30] diseases) will be added. In addition, current and previous treatment for either PsA or psoriasis will be noted. Severity and location of psoriasis (via Psoriasis Area and Severity Index [31] and body surface amount will be noted. Nail involvement will be assessed via Nail Psoriasis Severity Index [32] and Nijmegen Nail Psoriasis Activity Index Tool [33]. Three of the currently used screening questionnaires (ie, Psoriasis Epidemiology Screening Tool [PEST], Toronto Psoriatic Arthritis Screen [ToPAS], and Psoriatic Arthritis Screening and Evaluation [PASE]) will be used to collect clinical characteristics that have been previously discovered in their development [13-15].

### Statistics

#### Prevalence

The primary outcome of this study will be the point prevalence (number per 100 patients) of PsA in established patients with psoriasis. Sensitivity analyses will be performed by including or excluding patients with an uncertain diagnosis after 1 year, patients who refuse referral, or patients who are otherwise lost to follow-up.

#### Effect of Referral

The effect of referral on treatment changes, disease activity, and HR-QoL will be assessed qualitatively in an explorative descriptive matter. No formal statistical analyses will be applied.

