## Methods

### Aim

The aim of this study is to determine the number of patients with (untreated) PsA in a group of psoriasis patients in a dermatological outpatient clinic. Furthermore, we want to optimize the detection of PsA in patients with psoriasis in a dermatological outpatient clinic. For this purpose, we defined the following research questions.

The primary objective is to determine the prevalence of very early, newly-discovered, and known PsA in a cohort of patients with psoriasis treated at a dermatology outpatient clinic.

The secondary objectives include determining if, in newly diagnosed patients with PsA, PsA disease activity and quality of life differ before and 1 year after rheumatological referral in case of PsA; discovering clinical parameters that are associated with the presence of PsA in a cohort of patients with psoriasis; and using the aforementioned parameters to develop a new or enhance an existing screening tool for concomitant PsA in patients with psoriasis.

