#### Follow-up

Only those patients with a newly discovered PsA, as confirmed by a rheumatologist after referral, will be approached for follow-up after 1 year. At that moment, changes in treatment, disease activity, and health-related quality of life (HR-QoL) will be noted.

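### The objective asks whether disease activity and quality of life differ after referral, but the plan provides no measure of uncertainty and labels an uncontrolled change an effect

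*Protocol article*

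**What the plan says.** The Aim section lists, among the secondary objectives, determining whether in newly diagnosed patients "PsA disease activity and quality of life differ before and 1 year after rheumatological referral".

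The scores for this are numerical and are planned at both time points. Outcome Measures and the Effect of Referral section under Outcome Variables name PASDAS (with its joint, dactylitis and enthesitis scores), DLQI and PsAID12, at referral and 1 year later.

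The Effect of Referral section under Statistics then sets the analysis: "The effect of referral on treatment changes, disease activity, and HR-QoL" "will be assessed qualitatively in an explorative descriptive matter". The next sentence is "No formal statistical analyses will be applied".

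On who is followed, the Follow-up section says: "Only those patients with a newly discovered PsA, as confirmed by a rheumatologist after referral, will be approached for follow-up". Outcome Measures adds, for confirmed active PsA, that "treatment changes and their effect on disease activity will be noted".

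**The concern.** There are two separate problems, and they need different remedies.

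1. **Objective and analysis do not match.** Whether scores differ between two times is a question about numbers. A plan that describes the scores and rules out formal analysis can show what was observed. It cannot show how far the observed change is compatible with no change, or with a worthwhile one. In a small group that uncertainty is what a reader most needs.

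2. **The label is causal and the design is not.** Only referred patients with confirmed new PsA are followed, so there is nobody to compare them with. An improvement at 1 year could reflect rheumatological care, a treatment change by the dermatologist, natural fluctuation, or regression to the mean after selection on signs present at the visit. Calling the change an effect of referral invites a conclusion that the data cannot carry.

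At stake is how one secondary result will be read, in a study whose purpose is to argue for better referral.

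**Working it through.** **Is this a detail left to an analysis plan?** No. The protocol states a rule, that no formal analysis will be applied. An analysis plan that added intervals would sit uneasily with that sentence.

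**The plan's own figures.** Study Size uses 10 events per predictor:
- 5 predictors at 30% prevalence: 50 / 0.30 = 166.7, rounded up to 167.
- 10 predictors at 20% prevalence: 100 / 0.20 = 500.
- With 300 patients: 300 × 0.20 = 60 and 300 × 0.30 = 90 cases, so 6 to 9 predictors.

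All of these reproduce. They concern the logistic model only; no figure is given for the before-after objective.

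**Expected number of pairs.** The Introduction says about one in three PsA patients go unrecognised in the dermatology clinic. Applying that share to this cohort is an assumption:
- 60 / 3 = 20 and 90 / 3 = 30 pairs, before any loss.

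**Precision of a paired mean change.** In units of the SD of the change, the 95% CI half-width is t(0.975, n − 1) / √n.

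| Pairs | Half-width (SD of change) |
|---|---|
| 20 | 0.47 |
| 30 | 0.37 |
| 16 (20 less an assumed 20% loss) | 0.53 |
| 24 (30 less an assumed 20% loss) | 0.42 |

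Small numbers therefore make the interval wide, but they do not make it uninformative.

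**Can the change be attributed to referral?** Three statements bear on this:
- Follow-up is restricted to newly discovered, confirmed PsA, so there is no comparison group.
- Referral and Referral Criteria selects mainly on current signs: swollen joints, inflammatory enthesitis or inflammatory back pain. Other grounds for suspicion are allowed.
- Effect of Referral under Outcome Variables counts treatment changes started by the dermatologist as well as by the rheumatologist.

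**Could regression to the mean matter?** Under a normal model with no true change, the expected fall is (1 − ρ) × E[z | selected], where ρ is the correlation between repeat measurements. The documents give neither ρ nor the degree of selection, so both are assumed:

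| Assumed ρ | Top 50% selected | Top 10% selected |
|---|---|---|
| 0.9 | 0.08 SD | 0.18 SD |
| 0.7 | 0.24 SD | 0.53 SD |
| 0.5 | 0.40 SD | 0.88 SD |

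The range runs from negligible to large. It shows that regression to the mean cannot be dismissed, and also that its size here is unknown.

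**The case against.** The case for leaving the text alone has real force.

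- **Description is allowed.** A reader might infer that the plan forbids all statistics on these scores. It does not. It excludes formal analyses and plans an exploratory description, so means, medians and changes can be reported. This stands.
- **The objective is secondary and was not used to size the study.** Describing a small group is defensible if the objective says so. This stands in part: the objective as worded asks whether the scores differ, and an interval presented as exploratory needs no power calculation.
- **An interval does not cure the missing comparator.** This stands. A confidence interval quantifies chance variation only, which is why the relabelling is a separate change.
- **The protocol makes no causal claim elsewhere.** The objective speaks of a difference before and after, the Follow-up section speaks of changes, and neither the Conclusions nor the Discussion says that referral improved outcomes. A reader might infer that the authors intend a causal conclusion; the documents do not show that. What remains is the wording of two headings, the sentence under the second, and a phrase in Outcome Measures.
- **Regression to the mean is uncertain.** A reader might infer that a given part of any fall will be an artefact. The referral threshold is low, the diagnosis must then be confirmed by a rheumatologist, and nobody is selected on DLQI, so the argument does not carry directly to that score. This stands: it is possible, but its size cannot be derived from the documents.

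**Conclusion.** The point holds and is minor. The stated objective and the stated analysis do not match: the question is whether scores differ, and the plan supplies no measure of uncertainty with which to answer it. The causal label does not fit an uncontrolled change in selected patients who may also have had their treatment altered by the dermatologist.

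An interval would have a half-width of about 0.37 to 0.47 SD of the change with 20 to 30 pairs, and 0.42 to 0.53 SD after an assumed 20% loss. These figures rest on applying the one-in-three share to this cohort.

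The primary prevalence result and the referral-tool model are not affected.

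**What to change.** 1. **Statistics, Effect of Referral.** Replace the sentence excluding formal analysis with, for example: *In newly diagnosed patients, the paired change from referral to 1 year in PASDAS, PsAID12 and DLQI will be estimated with a 95% confidence interval. The number of patients without a 1-year value will be reported for each score. These estimates are exploratory and no hypothesis-testing claim will be made.* If the sponsor prefers description only, the objective in the Aim section should instead be reworded to describing the change.
2. **Labels.** Rename both sections to *Change after referral*, use the same term in the sentence that opens the Statistics section, and align the phrase in Outcome Measures about treatment changes and disease activity.
3. **Interpretation.** Add one sentence stating that the change cannot be attributed causally to referral, because there is no comparison group, patients are referred largely on signs present at screening, and other treatment changes may contribute.

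The cost is a few sentences and three intervals, which will be imprecise. No additional measurement is needed, since these scores are already planned at both time points.
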